**Methods and design::**

A single blind randomized controlled trial will be conducted. Sixty chronic insomnia volunteers and 30 healthy volunteers will be recruited for this study. Sixty insomnia volunteers will be randomly divided into a drug group and a massage group, and 30 healthy volunteers will be assigned to the healthy group. The manipulation of the treatment group will be mainly carried out through abdominal rubbing and vibration massage, once a day, 30 min/time, 5 days for a course of treatment, and a total of 4 intervention courses will be carried out. Patients in the drug group will be given orally spleen-invigorating bolus, twice a day, 1 pill in the morning and 1 pill in the evening. The course of treatment will be carried for 5 days, and a total of 4 courses of treatment will be administered.

The massage group will be compared with the healthy group and the drug group by Pittsburgh Sleep Index scale (PSQI), Hyperarousal scale (HAS), Hamilton Depression scale (HAMD), Fatigue scale-14 (FS-14), and Wechsler Adult Memory scale (WAIS) scales using to observe the sleep quality. Rs-fMRI will be used to observe various BOLD signals in the brain and compare the values of Reho, fALFF, and FC. MRS technology will be used to observe the contents of GABA and 5-HT in the hypothalamus. Additionally, the contents of cortical hormone releasing hormone (CRH), adrenocorticotropic hormone (ACTH), COR, GABA, NE, PGE2, and 5-HT in the serum will be also detected. The serum of each group will be taken for 1H nuclear magnetic resonance (^1^HNMR) metabolomics study to analyze the various common metabolites, differential metabolites, potential metabolic biomarkers, and metabolic pathways among the 3 groups. Finally, in combination with the brain functional imaging and brain spectrum, the potential mechanism of abdominal vibration and ring massage will be discussed.

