### Setting

2.2

The patients will be recruited from the Department of Zang-fu Massage, Affiliated Hospital of Changchun University of Chinese Medicine. Additionally, for participating in the trial, the patients will be screened strictly according to the diagnostic criteria, inclusion criteria, and exclusion criteria, and the requirements for the sample size estimation will be based on the clinical calculation formula employed for small sample size. The sample size (n = 16.76) will be calculated, that is, the therapeutic effect could be judged by the sample size of >16.67 people in each group. In this study, therefore 30 people will be observed in each group, which met the sample size estimation criteria.

The trial researcher will be able to record the subject's basic information (such as date of birth, sex) and answer patient trial screening questions. After the various patients have completed screening and enrolled, the trial study serial number, that is, the patient's unique identification number (SIN), will be obtained according to the enrollment time and order of enrollment, until the total number of observations (30 cases) was completed. Thirty healthy volunteers and 30 patients will be recruited for the study. After clinical evaluation and blood sampling, abdominal massage therapy will be adopted.

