### Participants and recruitment

2.3

The recruitment posters will be displayed in the hospitals and forward recruitment information will be posted on WeChat to recruit the potential participants for this study. The participants will be explained in detail about the potential benefits and services to be provided and the risks associated with participating in the study, including adverse clinical outcomes that may be associated with abdominal massage therapy. A detailed reading and an informed consent will be signed by each participant prior to the participation. On the consent form, participants will also be asked whether they provide consent to use their data even if they opt out of the trial. The participants will also be required to obtain permission for the research team to share relevant information with staff from the participating hospitals or regulatory agencies. The participants will receive 4 different courses of abdominal massage therapy. In addition, 30 healthy age- and sex-matched, volunteers with good sleep pattern will be recruited as the healthy controls. The personal information of all the participants will be kept confidential by the researchers and used only for this study.

The patients must properly understand and sign informed consent. Pittsburgh Sleep Index scale (PSQI), Hyperarousal scale (HAS), Hamilton Depression Scale (HAMD), and HAMA scores will be used to potentially determine whether participants meet the inclusion criteria. Patients who met the criteria will thereafter be included in the study (Fig. 1).

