#### Inclusion criteria for chronic insomnia (heart and spleen deficiency type)

2.6.1

The participants will have to meet the diagnostic criteria of chronic insomnia and the TCM symptoms of heart and spleen deficiency, and fulfill the following conditions: they will have to meet the diagnostic criteria for chronic insomnia, and meet the heart and spleen deficiency related symptoms of TCM. They must be between 50 and 55 years of age. They must not have been enrolled in any other clinical studies. They will have to sign informed consent and voluntarily participate in this research. Their Pittsburgh Sleep Index (PSQI) index score must be >7, the points of the Athens (AIS) scale score must be >6. The standard score of Depression Scale (SDS) and Anxiety Scale (SAS) must be ≤60. They must not experience work and life pressure during the observation period. They must not suffer from major cardiovascular and cerebrovascular diseases and other chronic diseases; their blood and urine analysis must be normal, as well as electrocardiogram, electroencephalogram, liver and kidney function test, blood sugar, and blood lipids and other inspection indicators must fall in the normal range. Patients with the above conditions lasting >1 year and frequency ≥3 times/wk will be included in this study.

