#### Inclusion criteria for healthy volunteers

2.6.2

Age 50–55, has been living in Changchun area, right-handed, moderate body size. They must have no religious belief, no tobacco, alcohol, coffee, tea, and other bad habits. They must be married with a moderate income. They must not be suffering from excessive pressure in work and life during the observation period. They must be in good health, and must not suffer from cerebrovascular disease and other chronic diseases. The woman must not be pregnant, menstruating, or lactating. The routine physical and chemical examinations such as ECG, hematuria routine, liver and kidney function, and other indicators must be normal. They must not display symptoms of insomnia, with PSQI, SAS, and SDS scores will have to be assessed as normal.

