### Statistical method

2.13

Spss23.0 statistical software will be used for statistical analysis for all the data generated. Chi-square test will be used for enumeration data, paired *t* test will be used for the comparison of measurement data before and after the treatment. One-way analysis of variance (ANOVA) will be used for comparison between the treatment groups, with *P* < .05 as difference and *P* < .01 as significant difference.

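### Healthy controls are sex-matched, but the named one-way ANOVA has no sex term, so the healthy-versus-patient tests are somewhat conservative

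*Protocol article*

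**What the plan says.** - **Matching.** Participants and recruitment (2.3): "30 healthy age- and sex-matched, volunteers with good sleep pattern will be recruited as the healthy controls". The section does not say whether matching is individual or by frequency, which patients the controls are matched to, or what the matching is for.
- **Between-group test.** Statistical method (2.13): "One-way analysis of variance (ANOVA) will be used for comparison between the treatment groups". No sex, age or matching term is named.
- **Other test for measurement data.** The same section: "paired *t* test will be used for the comparison of measurement data before and after the treatment". This pairs a person with himself or herself over time, not a patient with a control.
- **Thresholds.** "with *P* < .05 as difference and *P* < .01 as significant difference".
- **Use of the healthy group.** Abstract, Methods and design: "The massage group will be compared with the healthy group and the drug group" on the rating scales. The abstract gives 60 patients randomised to two groups, plus 30 healthy volunteers.
- **Age limits.** Patients (2.6.1): "They must be between 50 and 55 years of age". Healthy volunteers (2.6.2): "Age 50–55, has been living in Changchun area, right-handed, moderate body size".
- **Data at hand.** Setting (2.2) has the researcher "record the subject's basic information (such as date of birth, sex" and similar items.

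**The concern.** When two groups are matched on sex, sex no longer contributes to the difference between their means. A one-way ANOVA still counts sex variation as unexplained error. Its standard error is then larger than the real sampling variability of the difference, under individual or frequency matching alike. The test rejects less often than its nominal level and has less power than a model with a sex term.

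There is a second, separate gap. Thirty controls cannot each be paired with one of 60 patients, and no stratification of the randomisation by sex is described. If the controls mirror one arm, the other arm may differ from them in sex mix by chance, and an unadjusted ANOVA leaves that difference in the estimate.

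At stake are the comparisons of patients with healthy people on the scales and on the serum ELISA analytes, for which 2.13 is the only analysis route given. The images go to SPM12 (2.11.2) and the metabolomics to principal component and orthogonal partial least squares analysis (2.11.4), so they fall outside this point.

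**Working it through.** **No figure of the plan to reproduce.** The document states no sex effect, standard deviation, correlation or power. Its sample size (16.76, also written 16.67, per group) has no stated inputs and does not bear on this point. The sizes below rest on assumptions, shown as ranges.

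**Inputs.** From the document: 30 per group; threshold 0.05 (two-sided assumed). Assumed: a difference of d = 0.736 SD, which gives 80% power by a two-sample t test at 30 v 30; and R², the share of outcome variance explained by sex, from 0.01 to 0.30.

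**Step 1: age.** Uniform ages over 50–55 have an SD of 5/√12 = 1.44 years. Suppose age correlates 0.2 to 0.5 with an outcome over ages 18–65 (R² 0.04 to 0.25). Restricted to 50–55, the remaining R² is only 0.0005 to 0.004; starting from ages 30–60 it is 0.001 to 0.009. Omitting age therefore costs less than 0.5% of the standard error. Sex is the only matching factor likely to matter.

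**Step 2: standard error and power for sex.**

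- Inflation of the standard error when sex is left out: 1/√(1−R²) − 1.
- Expected standardised difference: 0.736 × √(30/2) = 2.85.
- Power with sex in the model: Φ(2.85/√(1−R²) − 1.96).
- Power without sex, standard calculation: Φ(2.85 − 1.96) = 81.3% (normal approximation; 80% by t test).
- Power without sex when sex is exactly balanced: Φ((2.85 − 1.96)/√(1−R²)). It is a little higher, because the difference itself then varies less than the ANOVA assumes.

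| R² of sex | SE inflation | Power with sex | Power without, standard | Power without, exact balance |
|---|---|---|---|---|
| 0.01 | 0.5% | 81.7% | 81.3% | 81.4% |
| 0.02 | 1.0% | 82.1% | 81.3% | 81.5% |
| 0.05 | 2.6% | 83.2% | 81.3% | 81.9% |
| 0.10 | 5.4% | 85.2% | 81.3% | 82.6% |
| 0.20 | 11.8% | 89.0% | 81.3% | 84.0% |
| 0.30 | 19.5% | 92.6% | 81.3% | 85.6% |

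For R² of 0.01 to 0.10 the loss is about 0.4 to 4 points against the standard figure, and about 0.3 to 2.6 points if matching is exact.

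**Step 3: true type I error of the unadjusted test under exact sex balance.** By formula, 2 × (1 − Φ(1.96/√(1−R²))) gives 4.4% at R² 0.05 and 2.8% at R² 0.20. Simulating 20,000 sex-matched 30 v 30 data sets gave 4.4% and 3.0%. A separate simulation of 3,000 data sets, assuming 70% women, gave 4.5% and 2.9% for sex differences of 0.5 and 1.0 residual SD. These differences correspond to R² = 0.21s²/(1 + 0.21s²) = 0.05 and 0.17. The error lies on the conservative side throughout.

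**Step 4: the arm not matched to the controls.** Assume 70% women and simple allocation. The difference in the proportion of women between two groups of 30 then has an SD of √(2 × 0.7 × 0.3/30) = 0.12. A sex difference of 1 residual SD would shift the unadjusted contrast by about 0.12 residual SD for a typical imbalance; a sex difference of 0.5 SD would shift it by about 0.06. A sex term removes this shift. The ANOVA does not, although its standard error allows for such chance imbalance on average.

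**The case against.** **Covariates are often left to the analysis plan.** This is a condensed article, and an unseen plan may adjust for sex. That limits the weight of the point but does not remove it: the article is not silent, it names a test, and the test has group as its only factor.

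**An unadjusted comparison of matched groups is legitimate.** In a non-randomised contrast, matching serves largely to balance confounders, and that balance survives the ANOVA. This stands for whichever patients the controls were matched to. It is not assured for each arm separately.

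**The loss is small and in the safe direction.** This stands. For PSQI, eligibility already separates patients from controls at baseline, so power there is hardly an issue. The objectives in 2.1 concern efficacy and mechanism of treatment, so the healthy contrasts are secondary.

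**Stronger readings that the document does not support.** A reader might infer that the matching was meant to gain precision and that the analysis defeats it; no purpose for the matching is stated. A reader might also assume a matched-pair correlation of 0.5 and conclude that the loss is large. With age confined to 50–55, that correlation would have to come from sex. With 70% women it would need 0.21s² = 1, a sex difference of about 2.2 residual SD, and nothing in the document suggests one. Nor do the thresholds become too lenient, since the test rejects too rarely.

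**Conclusion.** The point holds as a minor inefficiency. The design balances sex and the named test ignores it, so the massage-healthy and drug-healthy tests on scales and ELISA analytes are somewhat conservative, and a sex imbalance against an unmatched arm goes uncorrected. If sex explains 1% to 10% of variance, the standard error is 0.5% to 5.4% too large and the power loss is at most about 0.4 to 4 points at 30 v 30 and 0.736 SD. A loss well beyond that needs R² of about 0.2 or more. R², the effect size, the share of women and two-sidedness are all assumptions. The calculations also use a two-group contrast rather than the three-group ANOVA, and the conservatism is smaller where sex balance is looser than exact. The randomised massage-drug comparison does not depend on the matching.

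**What to change.** In 2.13, replace the one-way ANOVA for the healthy-versus-patient comparisons of scales and ELISA analytes with a linear model containing group and sex, with age in years optional. Report the adjusted massage-healthy and drug-healthy differences with 95% confidence intervals. Do not use a one-to-one paired test across matched people: 30 controls cannot be paired with 60 patients, and dropouts would break pairs.

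The cost is one sentence and one residual degree of freedom, or two with age. Sex and date of birth are already recorded, the SPSS software already named fits the model, and no further data or participants are needed.

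### As most likely read, the planned one-way ANOVA includes the non-randomised healthy volunteers, so its overall F test does not isolate massage versus drug, the only randomised contrast

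*Protocol article*

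**What the plan says.** Section 2.13 (Statistical method) gives chi-square for counts, a paired t test for before-after change, and for comparisons between groups: "One-way analysis of variance (ANOVA) will be used for comparison between the treatment groups". The threshold is given as "with *P* < .05 as difference and *P* < .01 as significant difference". No contrast or pairwise procedure is named.

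The Abstract (Methods and design) describes three groups. Two are randomised: "Sixty insomnia volunteers will be randomly divided into a drug group and a massage group". The third is not: "30 healthy volunteers will be assigned to the healthy group". It then sets out the comparison: "The massage group will be compared with the healthy group and the drug group by Pittsburgh Sleep Index scale (PSQI" and further scales.

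The entry criteria separate patients from volunteers on PSQI. Section 2.6.1 says of patients: "Their Pittsburgh Sleep Index (PSQI) index score must be >7". Section 2.6.2 says of healthy volunteers: "They must not display symptoms of insomnia, with PSQI, SAS, and SDS scores will have to be assessed as normal". Section 2.2 (Setting) gives the group size: "30 people will be observed in each group".

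**The concern.** Efficacy of the massage is the first objective in section 2.1, and massage versus drug is the only comparison that randomisation protects. A three-group F test asks whether all three means are equal. It rejects if patients differ from healthy people, whether or not the two treatments differ from each other. The other test for measurement data, the paired t test, works within a group and does not compare the arms either.

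Followed as written, section 2.13 could therefore yield a P value below its threshold that reflects only the contrast between insomniacs and good sleepers. A reader could take that P value as evidence about treatment.

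A secondary risk arises if a pairwise massage-drug test borrows its error variance from all three groups. The healthy group's spread would then enter the standard error of a comparison in which that group takes no part.

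**Working it through.** **Which groups enter the ANOVA.** Section 2.13 speaks of treatment groups, and the healthy volunteers receive no treatment in the Abstract. Taken literally, that means massage and drug, and a two-group ANOVA is the same as the two-sample t test. But the Abstract promises a comparison of massage with the healthy group on the scales, and 2.13 offers no other test for it. The three-group reading is therefore an inference, and the more likely one.

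**Overall F test with identical arms.** The article gives no SD or expected difference for any outcome, so there is no figure of its own to reproduce here. Inputs:

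- n = 30 per group (Abstract; section 2.2).
- Alpha = .05 and .01 (section 2.13).
- Massage mean = drug mean, and equal SDs (assumed).
- Patient-healthy gap of d SD at the time of analysis (assumed, shown as a range).

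With means (d, d, 0), the grand mean is 2d/3. The sum of squared deviations is 2(d/3)² + (2d/3)² = 2d²/3, so the noncentrality is 30 × 2d²/3 = 20d². Degrees of freedom are 2 and 90 − 3 = 87, with critical values 3.10 (.05) and 4.86 (.01).

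| Gap d (SD) | Noncentrality 20d² | Prob. P < .05 | Prob. P < .01 |
|---|---|---|---|
| 0 | 0 | 0.05 | 0.01 |
| 0.25 | 1.25 | 0.151 | 0.048 |
| 0.5 | 5.0 | 0.489 | 0.255 |
| 0.8 | 12.8 | 0.893 | 0.727 |
| 1.0 | 20.0 | 0.982 | 0.928 |
| 1.5 | 45.0 | about 1.00 | about 1.00 |

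**Pairwise massage-drug test on the three-group error.** Let r be the healthy SD divided by the patient SD. With equal group sizes, the pooled variance is (2 + r²)/3 times the patient variance, so the standard error is multiplied by √((2 + r²)/3). For r = 0.5 this is √(2.25/3) = 0.866. Type I error at nominal 5% was simulated with 200,000 runs per ratio and no true massage-drug difference:

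| r (assumed) | SE multiplier | Unadjusted test | Tukey | Two-arm error only |
|---|---|---|---|---|
| 0.25 | 0.829 | 0.104 | 0.052 | 0.050 |
| 0.5 | 0.866 | 0.088 | 0.042 | 0.049 |
| 0.75 | 0.924 | 0.069 | 0.030 | 0.050 |
| 1.0 | 1.000 | 0.051 | 0.019 | 0.051 |
| 1.25 | 1.09 | 0.033 | 0.011 | 0.050 |
| 1.5 | 1.19 | 0.020 | 0.006 | 0.050 |

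A separate run of 40,000 simulations with an assumed patient SD of 3 and healthy SD of 2.5 gave 0.063 for the unadjusted test, so the inflated range is about 6% to 10%. The direct two-arm test stays at about 5% throughout.

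**The case against.** The strongest objection is that 2.13 may mean only massage and drug, in which case the ANOVA is the right two-arm test and the problem disappears. That reading cannot be excluded. It leaves the healthy comparison promised in the Abstract without a test, so the section needs a clarifying sentence either way.

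Second, the Abstract does say that massage is compared with drug, and an ANOVA followed by pairwise tests is ordinary practice. A condensed article may leave the pairwise method to a fuller document. That is fair, and the absence of a named post-hoc test is not the point made here. The point is that the test and threshold actually stated do not, on the likely reading, address the randomised contrast.

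Third, the probabilities of 0.49 to 0.98 are power to detect a real patient-healthy gap. A reader might take them for false-positive rates of the massage-drug comparison, and they are not. They show how often the omnibus result would be significant while carrying no information about treatment. The article does not say that the omnibus P value will be reported as a treatment effect.

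Fourth, a reader might infer that pooling the variance necessarily makes the massage-drug standard error too small. The documents do not support that. It would take an unadjusted pairwise test on the three-group error, which is not named, and a healthy SD below the patient SD, and no SDs are given. A narrower healthy spread on PSQI is plausible because entry confines it to the normal range, but patient scores are also cut off from below. With equal SDs there is no distortion, with a larger healthy SD the test is conservative, and with Tukey the error does not exceed 0.052 at any ratio examined.

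Fifth, it is tempting to say that the group differences are fixed by the entry criteria for every outcome. They are built in for baseline PSQI only. For serum, spectroscopy, imaging and the other outcome scales, and for all values after treatment, the gap is unknown. Imaging and metabolomics also have their own methods in sections 2.11.2 and 2.11.4, so the point concerns univariate measurement data.

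**Conclusion.** The point holds on the three-group reading, which is the likely but not the certain one. The planned F test does not isolate massage versus drug. With identical arms and 30 per group, it is significant at P < .05 with probability 0.49, 0.89 and 0.98 for assumed patient-healthy gaps of 0.5, 0.8 and 1.0 SD. The stricter .01 level does not remove the problem. It fades only if both arms end close to the healthy mean. The variance effect is secondary and conditional: it can distort an unadjusted massage-drug test in either direction, or not at all.

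**What to change.** In section 2.13, state three things:

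1. The efficacy analysis is the direct comparison of massage with drug in the randomised patients only, using the error variance of those two arms, reported as a mean difference with a 95% CI.
2. Comparisons with the healthy volunteers are reported separately.
3. No treatment conclusion is drawn from any omnibus test that includes the healthy volunteers.

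Adjusting the two-arm comparison for the baseline value would be preferable, but the point does not depend on it. The cost is two or three sentences. No extra participants, visits or measurements are needed.

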#### Treatment rating scale

2.11.1

Based on the scale evaluation, PSQI, FS-14, HAS, and WAIS scales will be used to evaluate heart rate variability (HRV) of patients in each group before the first treatment, after the last treatment, and 4 weeks after the end of treatment (follow-up).

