#### Rs_fMRI

2.11.2

Sleeping patients will be subjected to Rs_fMRI in the morning of the day before the start of treatment and the morning after the last treatment after completion of the 4 courses of treatment. Siemens will be first used to perform conventional MRI structural images of the brain, namely T1 and T2 scans. The test will be terminated if the brain structure was abnormal. When the standard Rs_fMRI test will be performed, the patients will be required to lie down, be quiet, close their eyes, and try not to think when scanning is being conducted. The three-dimensional “∗.DCM” file will be obtained after scanning as per the parameters design of Siemens medical system, and the original data will be saved. The image will be preprocessed by DPARSF software including conversion of “.dcm ”to“.nfTI,” Slice Timing, head Timing (Realign), Normalize, Smooth etc. The pretreatment parameter TR will be set at 2 mm; the first 10 time points will be removed; FALFF Band (Hz): 0.01 to 0.1; ReHo Ouster: 27 Voxels. Voxel Slice [3,3,3], others with default values. SPM12 software will be used for statistical analysis of the images, and Xjview software will be used for image analysis.

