#### ELISA detection

2.11.5

The estimation of the serum CRH, CRHR1, ACTH, COR, GABA, NE, PGE2, 5-HT levels will be carried out using enzyme linked immunosorbent assay (ELISA). The serum samples will be prepared and processed according to the instructions of each ELISA kit to calculate the OD value and to calculate the content using the curve formula.

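### Section 2.13 sets a two-tier P rule for the group comparisons but names no primary outcome, lead comparison or multiplicity control across about 15 scalar outcomes

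*Protocol article*

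**What the plan says.** Section 2.13 of the protocol article opens with broad scope: "Spss23.0 statistical software will be used for statistical analysis for all the data generated". It plans two tests for continuous measures. Within groups, "paired *t* test will be used for the comparison of measurement data before and after the treatment". Between groups, "One-way analysis of variance (ANOVA) will be used for comparison between the treatment groups", and that sentence ends with the decision rule: "with *P* < .05 as difference and *P* < .01 as significant difference". No adjustment, ordering of outcomes or preferred group contrast follows.

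The measures are set out in section 2.11:
- Section 2.11.1 has "PSQI, FS-14, HAS, and WAIS scales will be used to evaluate heart rate variability (HRV) of patients in each group", at baseline, end of treatment and four weeks later. I read this as four scales and heart rate variability (HRV), each assessed as an outcome.
- Section 2.11.5 lists eight analytes: "The estimation of the serum CRH, CRHR1, ACTH, COR, GABA, NE, PGE2, 5-HT levels".
- Section 2.11.3 measures GABA and 5-HT in the hypothalamus by magnetic resonance spectroscopy (MRS).
- The abstract also plans to "compare the values of Reho, fALFF, and FC". Section 2.11.2 gives those data a separate route: "SPM12 software will be used for statistical analysis of the images". Section 2.11.4 sends the NMR spectra to multivariate software.

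Section 2.1 states the aims as efficacy and neural mechanisms without naming a measure. The sample size in section 2.2 is tied to no outcome.

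**The concern.** The article sets out to determine efficacy, yet it does not say which result would establish it. Under the rule as written, any one of about 15 measures falling below .05 can be reported as a difference between massage and drug, and the choice can be made after the results are known.

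The two tiers make this worse. A P value of .03 on the sleep scale would be a 'difference' but not a 'significant difference', and nothing says which grade supports an efficacy claim. The group contrast is open too. The abstract compares massage with both the drug group and the healthy group, so an overall ANOVA result could reflect insomnia versus health rather than one treatment versus the other.

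At stake is the error rate of the headline claim, which the plan leaves uncontrolled.

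**Working it through.** The article states no family-wise error rate, so there is no figure of its own to reproduce. The calculation below derives one from the stated rule.

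**Count of outcomes.** Scales in section 2.11.1: 4 (PSQI, FS-14, HAS, WAIS). HRV, counted as one measure: 1. Serum analytes in section 2.11.5: 8. MRS contents in section 2.11.3: 2. Total 4 + 1 + 8 + 2 = 15. Images and NMR spectra are left out.

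**Comparison.** Massage versus drug, 30 per arm, one test per outcome at end of treatment, no true difference on any outcome.

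**Independent tests.** The chance of at least one false positive in k tests at level α is 1 − (1 − α)^k.
- α = .05, k = 15: 1 − 0.95^15 = 1 − 0.463 = 0.537, about 54%. Expected number of false 'differences': 15 × 0.05 = 0.75.
- α = .01, k = 15: 1 − 0.99^15 = 1 − 0.860 = 0.140, about 14%.

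**Correlated tests.** The article gives no correlations, so I assume equal correlation between outcomes and show a range. Simulating two arms of 30 with 15 normal outcomes, tested at .05, gives:

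| Correlation between outcomes | Chance of at least one false 'difference' |
|---|---|
| 0 | about 54% |
| 0.3 | about 46% |
| 0.5 | about 37% |

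**Sensitivity to the count.** The abstract adds a depression scale (HAMD) that section 2.11.1 omits. With four scales and no HRV, k = 14 and 1 − 0.95^14 = 51%. With five scales and HRV, k = 16 and 1 − 0.95^16 = 56%.

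**Follow-up visit.** Testing the four scales and HRV again four weeks later adds 5 tests, so k = 20. Independent tests give 1 − 0.95^20 = 64%.

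**Paired t tests.** A before-after test for each of those 20 outcome-by-visit combinations in each of two patient arms adds 40, making 60 tests. I simulated these with no change over time, correlation 0.5 between repeated values of the same outcome, and .05 applied to the paired tests as well. At least one result fell below .05 in about 83% of runs when outcomes were correlated at 0.5. This last figure is only a bound on what the rule permits. A before-after change in one arm is not a treatment comparison, and patients selected for poor sleep may well change without any treatment effect.

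**The case against.** Several objections have force.

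**Images and spectra.** A reader might infer from the opening words of section 2.13 that voxels and metabolites will be tested at an uncorrected .05. The documents do not support that. The thresholds are attached to the ANOVA sentence, sections 2.11.2 and 2.11.4 route these data to other software, and no threshold is given there. Correction methods for such data are also commonly left to a fuller document. That part is not claimed.

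**'More likely than not'.** A reader might conclude that a false positive is more probable than not. For the 15 between-group tests this is true only at .05 and near independence. The article itself describes CRH, ACTH and cortisol as successive steps of one axis, so some correlation is to be expected, and at 0.3 the figure is already below one half. At .01 it is about 14% even with independent tests.

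**Global null.** The figures do not carry over to an ANOVA that includes the healthy volunteers. Patients need PSQI above 7 (section 2.6.1) and healthy volunteers must score normal (section 2.6.2), so a PSQI difference is built in by selection and would not be a false positive.

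**The second tier.** P = .03 does receive a stated grade, so the rule is not silent. What remains open is which grade carries the conclusion.

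**The unseen analysis plan.** It may hold multiplicity procedures. That answers a complaint about missing detail. It does not answer one about a decision rule that the article states without any lead outcome.

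**PSQI as lead.** The discussion frames the hypothesis around the hypothalamic-pituitary-adrenal axis, so the documents do not dictate PSQI. It is a reasoned choice: it measures sleep quality, is listed first and is an entry criterion.

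**Conclusion.** The point holds for the scalar outcomes. Section 2.13 gives a two-tier rule, and nothing in the article says which outcome, contrast or tier decides efficacy. For massage versus drug with no true effects, the chance of at least one false 'difference' at .05 is about 37% to 54% over 15 tests, for correlations from 0.5 down to 0. At .01 it is about 14% with independent tests.

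These figures rest on 15 outcomes, one end-of-treatment test each, 30 per arm and an assumed equal correlation. The follow-up visit and the paired tests push them up; stronger correlation pulls them down. No claim is made about voxel-wise or metabolite-wise testing. The need for a named lead outcome does not depend on where in the range the true figure lies.

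**What to change.** Before results are seen, amend section 2.13 to:
- name PSQI total score, massage versus drug at end of treatment, as the single primary outcome, tested two-sided at .05;
- remove the P < .01 tier;
- report the other scales, HRV and the follow-up visit as secondary, with confidence intervals;
- control the false discovery rate at 5% across the eight serum analytes;
- label the MRS, fMRI and metabolomics results exploratory.

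The error rate of the main claim is then 5%. If no analyte truly differs, a 5% false discovery rate also holds the chance of any false serum finding to about 5%.

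The change needs no new patients, visits or assays. It has two costs. Fewer secondary results will be called significant. The sample-size statement in section 2.2, which gives no outcome, effect size, standard deviation, alpha or power, should be tied to the named primary outcome.
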